**Age group (years)**			
	18-39	21 (17.9)	18 (15.4)
	40-59	19 (16.2)	19 (16.2)
	60-79	21 (17.9)	19 (16.2)
**Smoking**			
	Never	55 (47.0)	52 (44.4)
	Occasionally	4 (3.4)	2 (1.7)
	Daily	2 (1.7)	2 (1.7)
**BMI**			
	<25.0	43 (36.8)	29 (24.8)
	25.0-29.9	12 (10.3)	24 (20.5)
	≥30.0	6 (5.1)	3 (2.6)
**School education^b^**			
	≤9 years	5 (4.3)	4 (3.4)
	10-11 years	13 (11.1)	7 (6.0)
	≥12 years	43 (36.8)	45 (38.5)

^a^Of whole study population.

^b^Highest school-leaving qualiﬁcation, recoded to years spent in school.

## Discussion

### Principal Findings

Within the study, 117 participants completed the recruitment. After the subtraction of some errors in sample collection and measurements, 106 stool samples are available with corresponding data on common nutrition (30-day FFQ). In addition, 109 face-to-face 24-hour recalls were conducted (data on current nutrition), with corresponding urine samples and measured urine parameters. For 82 of these data sets, additional data on physical activity have been collected.

The 2 main aims of the study were to collect samples and data for (1) validating the dietary recall software GloboDiet and (2) for studying the association between diet and the intestinal microbiome. The 117 participants who successfully completed the study were equally distributed with respect to sex and age groups. However, the fraction of participants with a BMI above 25 kg/m² was lower in the study (females: 18/61, 29.5%, males: 27/56, 48.2%) than observed in the official representative statistics of the German population in 2017 (females: 43.1%, males: 62.1%, data set 12211-9018 in the Genesis database [44]). In addition, the average level of education is high in the study population. Therefore, the study population could be somewhat biased toward a healthier lifestyle, including nutrition and activity, than would be expected in the general population.

For the validation of the updated GloboDiet version, protein and potassium intake determined with the software will be compared with the excretion of protein and potassium in the 24-hour urine collection. In addition, EI calculated from the 24-hour recall will be compared to TEE and RMR. To estimate the validity of the current GloboDiet version, different methods will be applied, like the Wilcoxon-signed rank test to test if the differences between nutrient excretion and nutrient intake, as well as TEE and EI, are different from zero, Spearman rank correlation coefficients to assess the strength of the correlations, as well as Bland-Altman plots [45,46]. Bland-Altman diagrams are suitable for visualizing measurement differences. In addition, participants will be grouped into tertiles to assess the agreement in ranking participants regarding nutrient intake and excretion, as well as EI and TEE. Furthermore, for EI, cutoff values according to Goldberg et al [47] and Black [48] will be calculated for group levels as well as for individuals.

With the samples collected in this study, we plan to further analyze the association between habitual diet and gut microbiota. The microbiota analysis will include single parameters (alpha-diversity and abundance of single taxa), which will be compared with specific food groups or nutrient intakes to identify biologically significant associations. More complex data, like beta diversity of the microbiome and dietary patterns, will be compared by means of ordinations or group categories like enterotype and dietary pattern (using both a priori and a posteriori approaches, such as principal component and principal coordinate analysis, reduced rank regression, or dietary indices). Thereby, we also aim at identifying which level of dietary data yields potential explanations for the observed microbiota variations (eg, dietary pattern, food group, or nutrient level). As a similar composition of the gut microbiota can lead to different activities and functions of this complex and versatile ecosystem within the host, it is important to look not only at the present bacteria but also at the metabolites they produce. Therefore, the fecal content of short-chain fatty acids and bile acids will also be determined. Correlation analyses between nutrition parameters and these functional indicators of microbial activity will further enhance the obtained information on associations between the microbiome and nutrition.

Besides the 2 primary aims of the study, the set of valuable samples and data offers opportunities for further analyses. The availability of 24-hour urine samples with corresponding information on nutrient intake, for example, enables the search for biomarkers associated with specific foods or food constituents. This data can be further enhanced or validated using data from the KarMeN study that was previously performed at the MRI [40].

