### Analysis of Biomarkers in Urine

#### Overview

The validation of the German GloboDiet version will use an approach with nitrogen and potassium urinary excretion as biochemical markers for protein, as well as potassium intake [36,37]. Nitrogen and potassium excretion were chosen because errors are likely to be independent between the measurements of biomarkers and dietary intake [38,39].

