#### Nitrogen Content

Total urinary nitrogen was quantified by the Kjeldahl method using automated digestion and distillation units (Digestion Unit K-35, KjelFlex K360, Büchi). Concentrated sulfuric acid and Hg- and Se-free Kjeldahl catalyst tablets (Merck) were used for digestion. Titration was done with 0.05 M sulfuric acid. Individual urine volumes and an assumed specific gravity of urine of 1.020 g/mL were used to convert the nitrogen content into grams of nitrogen per 24 hours. The reference range for the specific gravity of urine is between 1.010 and 1.030 g/mL. The Karlsruhe Metabolomics and Nutrition (KarMeN) cohort [40] was used as the reference population.

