#### Sodium and Potassium Content

Sodium and potassium measurements were performed in an accredited clinical laboratory (MVZ Labor PD [name] and colleagues) using ion-sensitive electrodes.

In order to obtain the excreted urinary sodium and potassium amount per day, the respective concentrations (mmol/L) were converted into g/d while taking the volume of urine and the respective molar masses into account.

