## Results

Recruitment of potential participants involved an initial telephone screening of 230 people who were interested in participating, of whom 133 were selected based on exclusion criteria (Figure 2). After their assignment to the study, 16 subjects had to be excluded for various reasons (Figure 2). Overall, a total of 117 participants completed the 2 visits to the study center (Table 1, Multimedia Appendix 2).

For 109 participants (57 women and 52 men), food consumption and nutrient intake data, assessed by a face-to-face 24-hour dietary recall, are available. The participants were equally distributed among the age groups (18-39 years of age: 36; 40-59 years of age: 35; 60-79 years of age: 38). Urine samples collected during a 24-hour period were provided and suited for analysis in 109 cases (nitrogen and osmolality measurements failed in 2 cases that could not be validly reproduced).

ActiHeart records were not complete in 27 cases, mostly because of the detachment of the device or similar technical problems that resulted in measurements shorter than the required 24 hours. Physical activity data were obtained for 82 of the 109 participants for which urine and current food consumption data were collected.

Nearly all participants provided the requested stool samples, but a few reported irregularities during sampling (eg, potential contamination with toilet water) that led to the exclusion of the samples from further analyses. A final available number of 111 stool samples, each consisting of 2 replicates, were attained.

FFQs were completed by 106 participants (53 women and 53 men) who also provided valid stool samples, equally distributed over the age groups (18-39 years of age: n=37; 40-59 years of age: n=31; and 60-79 years of age: n=38).

**Table 1 table1:** Study population characteristics (N=117).

Characteristics		Female participants, n (%)^a^	Male participants, n (%)^a^

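### Protein and potassium intake are tested for zero difference from urinary excretion, with no stated conversion of excretion to an intake equivalent

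*Protocol article*

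**What the plan says.** The Overview of the urine biomarker section in the Methods names "nitrogen and potassium urinary excretion as biochemical markers for protein, as well as potassium intake", and cites sources for the approach. "Total urinary nitrogen was quantified by the Kjeldahl method"; urine volume and an assumed specific gravity "were used to convert the nitrogen content into grams of nitrogen per 24 hours". For potassium, "the respective concentrations (mmol/L) were converted into g/d while taking the volume of urine and the respective molar masses into account". Both descriptions end at an excreted amount.

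The planned analysis is in the Discussion under Principal Findings. There, "protein and potassium intake determined with the software will be compared with the excretion of protein and potassium in the 24-hour urine collection". Among the methods listed is this one: "Wilcoxon-signed rank test to test if the differences between nutrient excretion and nutrient intake, as well as TEE and EI, are different from zero". Beside it stand Spearman correlation, Bland-Altman plots and agreement by tertile. No acceptance criterion is attached to any of them.

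**The concern.** The comparator (excretion) and the null value (zero) are both stated. They fit together only if everything eaten is recovered in urine. If some nitrogen and potassium leaves by faeces, sweat or skin, an error-free recall should exceed urinary excretion, and a difference of zero would indicate under-reporting.

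The energy reference is treated differently. Total energy expenditure is built from resting metabolic rate, activity and diet-induced thermogenesis, so it is meant to be complete. No corresponding step appears for protein or potassium, and the Limitations do not mention non-urinary losses.

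What is at stake is the estimate of systematic over- or under-reporting of these two nutrients. Of the listed methods, only the zero-difference test and the Bland-Altman bias address it for protein and potassium, and both would be shifted.

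**Working it through.** **Plan's own figure.** There is none on this point. The only stated power (above 0.998) concerns energy intake against energy expenditure. Its effect size is given as a formula without a value, so it cannot be reproduced, and it does not bear on protein or potassium.

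**Inputs from the article.** "Urine samples collected during a 24-hour period were provided and suited for analysis in 109 cases", so n = 109 for potassium. Nitrogen failed in 2 of these, so n = 109 - 2 = 107 for protein. The significance level of .05 is stated for the energy test and is assumed here for the nutrient tests.

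**Inputs assumed, not in the documents.** Urinary recovery R = 0.75 to 0.90; true protein intake 80 g/d; SD of the paired differences 20-35 g/d for protein and 30-50% of mean intake for potassium. A nitrogen-to-protein conversion is taken as made, since grams of protein and grams of nitrogen cannot otherwise be subtracted.

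**Formulas.** For an unbiased recall:

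- expected difference = intake × (1 - R)
- z = difference / (SD/√n)
- probability of a significant difference ≈ 1 - Φ(1.96 - z)

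| Nutrient | R | Difference | SD | z | Probability |
|---|---|---|---|---|---|
| Protein, n=107 | 0.80 | 80 × 0.20 = 16 g | 20 g | 16/(20/√107) = 8.3 | >0.99 |
| Protein, n=107 | 0.80 | 16 g | 35 g | 16/(35/√107) = 4.7 | >0.99 |
| Protein, n=107 | 0.90 | 80 × 0.10 = 8 g | 35 g | 8/(35/√107) = 2.36 | 0.66 |
| Potassium, n=109 | 0.90 | 10% | 50% | 0.10/(0.50/√109) = 2.09 | 0.55 |

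The two rows at R = 0.90 are the low ends of the assumed ranges. At R = 0.75 the probability is about 1.00 for both nutrients.

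**Opposite case.** A recall that captures a fraction R of true intake has expected difference R × intake - R × intake = 0. At R = 0.80, 20% under-reporting of 80 g/d gives 64 g/d, equal to the urine equivalent.

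**Check with the planned test.** The two-sided signed-rank test was simulated at n = 107 and 109, with 1,000 runs per setting, a between-person CV of true intake of 30%, and independent errors of 20-40% CV in both recall and urine (all assumed).

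| R | Unbiased recall, uncorrected: significant | Under-reporting by 1-R, uncorrected: significant | Under-reporting by 1-R, after dividing by the true R: significant |
|---|---|---|---|
| 0.90 | 48-96% | 3-6% | 48-96% |
| 0.80 | 98-100% | 4-6% | 97-100% |
| 0.70 | 100% | 4-6% | 100% |

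After division by the true R, an unbiased recall is flagged in about 3-6% of runs, close to the nominal 5%. A paired-t calculation with SD of the difference at 30-60% of mean intake gives 0.93-1.00 at R = 0.80 and 0.40-0.93 at R = 0.90, so the widest spread falls somewhat below 0.5.

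**What does not move.** A constant factor leaves ranks unchanged. Spearman's coefficient was 0.416 before and after scaling in a simulated sample, and tertile membership is unchanged for the same reason. The energy comparison does not use urinary excretion.

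**The case against.** The strongest reply is that uncorrected use is read from a condensed article. The analysis paragraph is a short passage in a Discussion, its list of methods is introduced as examples, and the Methods cite sources for the biomarker approach that are not at hand. The laboratory sections would properly stop at excreted amounts even if a later step derived intake from them. Some nitrogen-to-protein conversion must be intended although none is written, so a recovery adjustment could be intended too. All of this stands, and it limits how firmly the point can be put. It does not remove it, because the published text names both the comparator and the null value, and that pair is wrong whenever recovery is below 100%.

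It is also fair that Spearman correlation and tertile agreement are untouched. They give no protection here, however, since neither can detect a constant bias.

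A reader might infer that a perfectly valid recall is bound to fail validation and an under-reporting one to pass. The article does not support that. It sets no pass/fail rule, and a significant difference is near-certain only at about 80% recovery or lower. A reader might also take the reference to excreted protein to mean that urinary protein was assayed. The Methods are clear that total nitrogen was measured, so this is loose wording.

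**Conclusion.** Wrong as written, but short of a must-fix. Taken literally, the zero-difference test and the Bland-Altman bias for protein and potassium are centred on the wrong value if urinary recovery is incomplete. Under an assumed recovery of 75-90%, an unbiased recall would show a significant apparent over-estimate in roughly 0.5 to 1.0 of studies of this size. Under-reporting by the unrecovered fraction would be flagged only at about the nominal error rate.

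The size rests on recovery fractions, intakes and SDs that the documents do not give, and on no correction being made. The full analysis plan is not shown and may contain one, which is why the severity is held down.

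**What to change.** In Principal Findings, replace the comparison with excretion by a comparison with biomarker-estimated intake:

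- protein = urinary N × nitrogen-to-protein factor / N recovery fraction
- potassium = urinary K / K recovery fraction

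Apply the signed-rank test and the Bland-Altman analysis to these quantities. State the factors and their sources, fix them before analysis, and repeat with a low and a high plausible recovery fraction. Fixing them first matters because the samples are already collected. With a urine equivalent of 64 g/d protein, the reference is 64/0.90 = 71 g/d at 90% recovery and 64/0.75 = 85 g/d at 75%. Refer to protein intake estimated from urinary nitrogen, not to excreted protein. If the full analysis plan already contains this step, aligning the article's wording with it is enough.

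The cost is a nitrogen-to-protein factor, two recovery fractions and a sensitivity table. No new data are needed, and the Spearman, tertile and energy analyses stay as they are.

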### Limitations

The study population was not recruited representatively. Therefore, the average BMI of study participants was lower than generally observed in the German population, indicating a potential bias toward healthier nutrition and lifestyles among the participants. With regard to recruitment, the focus was based on the sample size of the study population needed for the validation of the 24-hour recalls. A total of 50 women and 50 men provided sufficient statistical power for the planned analyses. However, the number of participants was comparatively low for the analysis of the microbiome, limiting the resolution to identify fewer common associations, for example, between nutrition and microbial features. Microbiome analysis based on 16S-rRNA genes is limited to identifying taxonomic composition, but available samples offer opportunities to measure metabolite concentrations or sequence the metagenomes to enable deeper insights.

A further limitation is that TEE was not measured using a doubly labeled water technique. This method has been shown to provide an accurate measure of the TEE [49-51]. At the time when the study was conducted, the use of doubly labeled water was not possible due to time and cost constraints.

### Comparison With Prior Work

During the KarMeN study, the metabolomes of blood and urine samples from 301 participants were analyzed, enabling the identification of biomarkers for dietary intake [40]. In comparison, while lacking blood samples, ErNst includes urine samples that are available for metabolomics and adds the opportunity to measure the intestinal microbiome and metabolome using the collected stool samples.

### Conclusions

We completed the recruitment and collection of samples and data for the ErNst study with a high degree of standardization. This enables the validation of the GloboDiet software, which will be used in the German National Nutrition Monitoring. In addition, microbiome composition and nutritional patterns will be compared to investigate functional associations and potential biomarkers.

## Appendix

Multimedia Appendix 1 List of primers used for amplification and sequencing of the V4 region of the prokaryotic 16S-rRNA gene.

Multimedia Appendix 2 Overview of availability of samples and data points per study participant.

## Abbreviations

AEE: activity energy expenditure
DIT: dietary induced thermogenesis
EE: energy expenditure
EFSA: European Food Safety Authority
EI: energy intake
ErNst: Erfassung der Energie- und Nährstoffzufuhr
FFQ: food frequency questionnaire
KarMeN: Karlsruhe Metabolomics and Nutrition
MRI: Max Rubner-Institut
PCR: polymerase chain reaction
RMR: resting metabolic rate
TEE: total energy expenditure
